### Interim analyses

Not applicable: no interim analyses will be performed, and no stopping guidelines will be established.

### Methods in analysis to handle protocol non-adherence and any statistical methods to handle missing data

We will utilize complete-case analysis for all endpoints and objectives. For post 6-session and/or post 12-session/follow-up data to be included in the analysis, participants must attend a minimum of 5 out of 6 ISF-NFB sessions in each respective 6-session block. Further, we will report the number and percentages of withdrawal in each of the groups. Based on our lab group’s prior feasibility study using ISF-NFB in an obese female population [159], discontinuation/loss-to-follow-up following randomization is expected to be 10-15%.

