### Criteria for discontinuing or modifying allocated interventions

Participants will be advised that they were able to withdraw at any time without giving a reason or may be withdrawn by the lead investigator if they (1) experience significant adverse effects that were deemed detrimental to their well-being or (2) are unable to adhere to protocol (e.g. missed >1 training session in either 6 session block, started or modified first-line therapies).

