### Plans to promote participant retention and complete follow-up

Once enrolled, every reasonable effort will be made to follow participants throughout the entirety of the study period via ongoing email and text messaging correspondence. In the event of premature discontinuation of the study for any reason, participants will be made aware that all data collected up to the point of withdrawal may be used for analyses.

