### Relevant concomitant care permitted or prohibited during the trial

Participants were asked to maintain any current first-line mental health therapies (e.g. pharmacotherapy) for the entire length of the trial period (i.e. baseline through follow-up). Any changes or introductions of first-line therapies (e.g. altered pharmacotherapy dosages, introduction of intensive psychotherapy) will render participants ineligible.

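### The only analysis set named is complete cases who attended at least 5 of 6 sessions, which can bias the Objective 1 comparison with sham

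*Protocol article*

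**What the plan says.** The section on non-adherence and missing data in the Protocol article sets one rule: "We will utilize complete-case analysis for all endpoints and objectives". It adds an attendance condition for post-6 and for post-12 and follow-up data: "participants must attend a minimum of 5 out of 6 ISF-NFB sessions in each respective 6-session block". It promises a count of withdrawals by group, and it expects that "discontinuation/loss-to-follow-up following randomization is expected to be 10-15" per cent.

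Other sections also remove participants after randomisation. Under Criteria for discontinuing or modifying allocated interventions, the lead investigator may withdraw someone for significant adverse effects or for non-adherence, with the examples "missed >1 training session in either 6 session block, started or modified first-line therapies". Under Relevant concomitant care, starting or changing first-line therapy "will render participants ineligible". Under Plans to promote participant retention, participants are told that "all data collected up to the point of withdrawal may be used for analyses".

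Statistical considerations names one sensitivity analysis for Objective 1, an ANCOVA with a linear baseline adjustment. Trial design describes a randomised superiority trial with 2:1:1 allocation (sham:ISF1:ISF2).

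**The concern.** Attendance, withdrawal for adverse effects and changes of therapy all happen after allocation. In people with anxiety and depressive disorders each may be related to how the participant is doing, which is what the HADS measures. Objective 1 attributes any improvement beyond sham to specific effects of training. That attribution relies on the arms being comparable, and a set selected on post-randomisation behaviour no longer guarantees it.

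The attendance condition also presupposes that a participant can have an outcome and still have attended too few sessions. That person's outcome is set aside although it was collected and although participants are told it may be used. With 15 per active arm, one or two such exclusions can move an arm mean noticeably.

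**Working it through.** **Figure to reproduce.** The article makes no sample-size or power calculation and gives no SD, so there is no stated figure to reproduce. The arm sizes are consistent: 60 split 2:1:1 gives 30, 15 and 15, as in the Abstract.

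**Inputs from the document.** N = 60; arms 30/15/15; expected loss 10–15%; ROPE ±0.1 for standardised mean differences.

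**Inputs assumed.** g, the difference in SD units between those kept and those dropped, and the split of losses between arms. The document gives neither.

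**Number lost at the stated rate.** 60 × 0.10 = 6 and 60 × 0.15 = 9, leaving 54 to 51 analysed. If proportional, sham loses 3 to 4.5 of 30 and each active arm 1.5 to 2.25 of 15.

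**Shift in one arm's mean.** With a fraction p dropped, mean(all) = (1 − p) × mean(kept) + p × mean(dropped). Hence mean(kept) − mean(all) = p × [mean(kept) − mean(dropped)] = p × g.

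| p | g = 0.5 | g = 1 |
|---|---|---|
| 0.10 | 0.05 SD | 0.10 SD |
| 0.15 | 0.075 SD | 0.15 SD |

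This assumes that the other arm's dropped participants resemble those kept. One exclusion in an arm of 15 at g = 1 shifts the mean by 1/15 = 0.067 SD, and two shift it by 2/15 = 0.133 SD.

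**Shift in the contrast when both sides lose people.** With g = 1 on both sides, 30 sham against 30 pooled active, the shift is (active lost − sham lost)/30.

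| Total lost | Sham | Active | Shift |
|---|---|---|---|
| 6 | 3 | 3 | 0 |
| 6 | 2 | 4 | 2/30 = 0.07 SD |
| 9 | 2 | 7 | 5/30 = 0.17 SD |
| 9 | 7 | 2 | −5/30 = −0.17 SD |

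The bias can be zero and can take either sign.

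**Against sampling error.** The unadjusted standard error for sham against one active arm, with equal variances, is √(1/30 + 1/15) = 0.316 SD. A shift of 0.05–0.15 SD is 0.16 to 0.47 of that.

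**The missed-session rule.** The drop-out criteria under Eligibility criteria count more than one missed session and mention no block. The discontinuation section counts "missed >1 training session in either 6 session block", and the missing-data section also works per block. Within the first block the three agree, because missing two or more of six means attending four or fewer. They part for someone who misses one session in each block: two missed in total is a drop-out under the first, while 5 of 6 twice is retained under the others.

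**The case against.** The strongest reply has five parts.

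- **Pilot status.** The Sample size section limits the trial to potential efficacy. That limits what may be concluded, but the sham contrast will still be read as the signal.
- **Blinding and reporting.** Participants are blinded, which should make loss less dependent on arm, and withdrawals will be reported by group. Both help. However, the trainer is unblinded and monitors adherence, and a count of withdrawals describes the loss without correcting for it.
- **The loss figure.** The 10–15% has no time point and most naturally covers the whole trial, whereas Objective 1 is assessed after about two weeks of training. It also counts people who leave, not observed outcomes set aside by the attendance rule, and that number is unknown. This stands, so the calculation is an illustration only. In the other direction, the EEG and ECG quality exclusions add loss for those endpoints.
- **Therapy changes.** A reader might infer that a change of therapy erases a participant's earlier data. The document does not say so. Withdrawal is discretionary, and participants are told that data up to withdrawal may be used, so someone who changes therapy after the post-6 visit may still count for Objective 1.
- **An unseen analysis plan.** A fuller plan might name another analysis set. The article nevertheless states its rule for every endpoint and objective, so this is not a detail left open.

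**Conclusion.** The point holds as a risk of bias. The only analysis set named is selected on events after randomisation, and no analysis as randomised stands beside it. At 10–15% dropped from one arm and an assumed difference of 0.5–1 SD, that arm's mean shifts by 0.05–0.15 SD. The upper part of that range reaches or passes the ROPE half-width of 0.1 SD; the lower part does not.

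Two stronger readings are not supported. A reader might infer that the rule does bias the comparison, or that it favours active training. Neither follows, because equal and equally selective loss gives no bias and the sign reverses if sham loses more of its poor responders. A reader might also say that the shift covers the whole ROPE. The ROPE of ±0.1 is 0.2 SD wide, so 0.10–0.15 SD covers the half-width only.

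The inconsistent missed-session rule is real but separate. It can affect only the post-12 and follow-up objectives, and adds no weight to the concern about Objective 1.

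**What to change.** 1. Make the main Objective 1 analysis all randomised participants in their allocated arm, with every observed post-6 outcome, regardless of sessions attended or therapy changes. Use the Bayesian random-effects model already planned.
2. Keep the 5-of-6 complete-case set as a supplementary analysis.
3. Add a simple sensitivity analysis for outcome-dependent missingness. For example, shift the assumed post-6 mean of those without that visit over a stated range, separately by arm. This is needed because such participants have only baseline data, so a missing-at-random model adds little for them.
4. Separately, reconcile the drop-out criteria under Eligibility criteria with the discontinuation and missing-data sections on how missed sessions are counted.

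The cost is wording and a few extra model runs. The downside is that the as-randomised effect may be slightly smaller than the one in good attenders. The fix does not rely on further data collection. Trial status expected that to finish by the end of 2021, and a remote questionnaire could not recover the EEG outcomes in any case.

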### Adverse event reporting and harms

We will systematically monitor adverse effects from the therapy for the duration of the trial using the Discontinuation-Emergent Signs and Symptoms checklist (DESS [309]) created, verbatim, in Qualtrics and completed by participants on an iPad during EEG set-ups in the interventional and post-interventional phases. Initially developed for drug trials [309], the DESS is a structured 43-item self-report that utilizes the following scale: 1=new symptom, 2=old symptom but worse, 3=old symptom but improved, 4=old symptom but unchanged, 5=symptom not present. The DESS has been used for the assessment of treatment-related side-effects in ID populations [310, 311] and, recently, has been employed to monitor adverse-effects specifically associated with NFB therapy [312]. Participants may be withdrawn from the trial by the investigators, even without their request, in the event of serious adverse effects. As detailed in the PIS, a brief (4-item) interview used during our group’s prior sLORETA ISF-NFB feasibility trial revealed that, although unusual or vivid dreams were experienced by some participants, there were no serious adverse effects [160].

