**Methods:**

We will randomly assign participants who meet the criteria for MDD, GAD, and/or SOC per the MINI (Mini International Neuropsychiatric Interview for DSM-5) to one of three groups: (1) 12 sessions of posterior cingulate cortex (PCC) ISF-NFB up-training (*n*=15), (2) 12 sessions of concurrent PCC ISF up-training and dorsal anterior cingulate cortex (dACC) ISF-NFB down-training (*n*=15), or (3) 6 sessions of yoked-sham training followed by 6 sessions genuine ISF-NFB (*n*=30). Transdiagnostic PROs (Hospital Anxiety and Depression Scale, HADS; Inventory of Depression and Anxiety Symptoms – Second Version, IDAS-II; Multidimensional Emotional Disorder Inventory, MEDI; Intolerance of Uncertainty Scale – Short Form, IUS-12; Repetitive Thinking Questionnaire, RTQ-10) as well as resting-state neurophysiological measures (full-band EEG and ECG) will be collected from all subjects during two baseline sessions (approximately 1 week apart) then at post 6 sessions, post 12 sessions, and follow-up (1 month later). We will employ Bayesian methods in R and advanced source-localisation software (i.e. exact low-resolution brain electromagnetic tomography; eLORETA) in our analysis.

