### Trial design

This study is a randomized, double-blind (participants and assessors), yoked-sham controlled (playbacks of genuine ISF-NFB sessions from another female ID participant at the same training stage), parallel-group (3-arm = sham, ISF-1, ISF-2), superiority, pilot trial with an allocation ratio of 2:1:1 (sham:ISF1:ISF2).

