### Randomization

Following baseline #2 measurements, participants were randomized to one of 3 arms: (1) yoked-sham, (2) ISF1 = PCC up-training, or (3) ISF2 = concurrent PCC up-training and dACC down-training. Sham participants were offered active ISF-NFB upon their completion of the trial, thereby minimizing the potential of sham trial-associated participation barriers [202] as well as addressing any potential ethical concerns of sham-only allocations.

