### Participant timeline

The trial period for each participant will be approximately 10 weeks and consist of one 30-min screening interview, two 60-min baseline assessments approximately 1 week apart, six 30-min genuine or sham ISF-NFB sessions (3× per week over 2 consecutive weeks) starting within 1 week after baseline #2, a 60-min post 6 sessions assessment, six 30-min genuine ISF-NFB sessions (3× per week over 2 consecutive weeks), a 60-min post 12 sessions assessment, and a 60 min 1-month follow-up assessment (Table 2 and Fig. 2). All post-treatment assessments and procedures will be identical to those performed at baseline.

**Table 2 Tab2:** Schedule of enrollment, interventions, and assessments

	T0	T1	T2	Allocation	T3-8	T9	T10-15	T16	T17
Enrollment									
Eligibility screen (MINI)	✓								
Informed consent	✓								
Anthropometric measures	✓								
Assessments									
PROs		✓	✓			✓		✓	✓
EEG		✓	✓			✓		✓	✓
ECG		✓	✓			✓		✓	✓
DESS					✓		✓	✓	✓
Blinding integrity						✓			
Groups									
Active	✓	✓	✓	✓	✓	✓	✓	✓	✓
Sham	✓	✓	✓	✓	✓	✓			

*Abbreviations*: *MINI* Miniature International Neuropsychiatric Interview, *PROs* patient-reported outcomes, *EEG* electroencephalography, *ECG* electrocardiography, *T0* interview, *T1* baseline #1, *T2* baseline #2, *T3–8* neurofeedback sessions 1 through 6, *T9* post 6^th^ session assessments, *T10–15* neurofeedback sessions 7 through 12, *T16* post 12^th^ session assessments, *T17* 1-month follow-up assessments

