### Statistical considerations

#### Objective 1

Between-group (sham vs. ISF1 and ISF2) comparisons post-6 sessions will be performed for the PROs and neurophysiological measures. For this analysis, we will use LORETA-Key software and a Bayesian model with random effects to allow for baseline differences and non-specific temporal effects between participants. A sensitivity analysis will be carried out to compare this approach with an ANCOVA that includes a linear baseline adjustment.

#### Objective 2

Regression methods will be used to explore the relationship between changes in the primary PRO subscales (i.e. HADS-A, HADS-D) and targeted ROI activity and connectivity for all participants post 6 sessions.

#### Objective 3

Within-group (ISF1 and ISF2) comparisons between post-6 sessions and post-12 sessions will be performed for all outcome measures. The same model will be applied as in Objective 1 where random effects will now allow for post-6 session differences between participants.

#### Objective 4

Within-group (ISF1 and ISF2) comparisons between post-12 sessions and 1-month follow-up will be performed for all outcome measures. This will use the same model as Objective 1 where random effects will now allow for post 12-session differences between participants.

#### Objective 5

Regression analysis from Objective 2 will be extended to post 12-session and 1-month follow-up for the ISF1 and ISF2 groups.

Analyses were performed using LORETA-KEY software, R, JAGS [299] and Stan [300] with analysis-specific details described below. For all endpoints, responses were modelled assuming a normal distribution (e.g. with group-specific means and variances or via regression). When normality assumptions were not met, appropriate transformations were performed. Additionally, potential endpoint covariates were examined (e.g. age); however, none exhibited correlations that were strong enough to warrant inclusion for denoising purposes in the models. For the Bayesian analysis, JAGS or Stan was linked to R using the rjags or rstanarm library with estimates based on 3 chains of 25,000 iterations with a burn-in/warm-up = 10,000 iterations. Vague priors were used throughout.

Bayes’ theorem postulates that the probability of an event A given event B is proportional to the probability of event B given event A multiplied by the prior probability of event A:$$P\left(A|B\right)\propto P\left(B|A\right)\ast P(A)$$

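### Table 2 schedules no DESS form at T9, so session 6 harms are picked up later in the active arms and, if the sham arm ends at T9, not at all in sham

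*Protocol article*

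**What the plan says.** Under Adverse event reporting and harms, the protocol article states "We will systematically monitor adverse effects from the therapy for the duration of the trial". The tool is the DESS, a 43-item self-report, "completed by participants on an iPad during EEG set-ups in the interventional and post-interventional phases".

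Table 2 (Participant timeline) ticks DESS at T3–8, T10–15, T16 and T17. The T9 cell is blank. T9 is defined as the "post 6^th^ session assessments", and PROs, EEG, ECG and the blinding questionnaire are all ticked there.

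The first objective's sham comparison is made at that visit: "Between-group (sham vs. ISF1 and ISF2) comparisons post-6 sessions will be performed for the PROs and neurophysiological measures" (Statistical considerations, Objective 1). Objectives 3 to 5 concern ISF1 and ISF2 only.

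The article gives two accounts of the sham arm after session 6:

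- The abstract's Methods paragraph describes "6 sessions of yoked-sham training followed by 6 sessions genuine ISF-NFB", and the Participant timeline text gives six genuine or sham sessions followed by six genuine ones.
- The Sham row of Table 2 ends at T9, and the Randomization section says "Sham participants were offered active ISF-NFB upon their completion of the trial".

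**The concern.** The harms text and the schedule do not agree. T9 has an EEG set-up and follows the first training block, so the wording of the harms section covers it, yet the table leaves it out. DESS is ticked at the corresponding visit after the second block (T16), and no reason is given for treating T9 differently.

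The blank cell matters because of when in a visit the form is completed. A form filled in at set-up reports on what happened before that day's session, so session 6 needs a later form. T9 is the first visit that could supply one, and it is the last visit in Table 2 that all three arms share. What is at stake is whether harms from the full sham-controlled block are ascertained in the same way in every arm. With no data monitoring committee and no auditing planned, the DESS is the only systematic harms instrument that the article describes.

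**Working it through.** There is no figure in the plan to reproduce. The check maps each training session to the first later visit that has a scheduled DESS.

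**Inputs**

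- DESS visits: T3–8, T10–15, T16, T17 (Table 2). Each row examined has all nine columns, and the PRO and blinding ticks fall on T9 as expected, so the blank cell is not a misaligned column.
- Sessions 1 to 6 are T3 to T8; sessions 7 to 12 are T10 to T15 (Table 2 footnote).
- The form is completed during EEG set-up (harms section). Cap fitting and gel come before training (Intervention descriptions).
- Sham n=30, ISF1 n=15, ISF2 n=15 (abstract), in line with 2:1:1 allocation of 60.
- Assumption: each form picks up effects arising since the previous form. The article does not state a recall period.

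**Mapping**

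| Session | ISF1 and ISF2 | Sham, if the arm ends at T9 | Sham, if genuine sessions follow |
|---|---|---|---|
| 1 to 5 | T4 to T8 | T4 to T8 | T4 to T8 |
| 6 | T10 | none | T10 |
| 7 to 11 | T11 to T15 | not applicable | T11 to T15 |
| 12 | T16 | not applicable | T16 |

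The last column assumes that the DESS schedule also applies to sham participants who continue. The T3 form precedes any exposure in every arm.

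**Size if the sham arm ends at T9**

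- Uncovered share: 1/6 = 16.7%, about 17%.
- Uncovered sham sessions: 30 × 1 = 30 of 30 × 6 = 180.
- Active arms in block 1: 30 participants × 6 = 180 sessions, of which 30 × 5 = 150 are covered at T4–T8 and 30 × 1 = 30 at T10. None is lost.
- Forms covering block 1: six per active participant (T4–T8 and T10) and five per sham participant (T4–T8). For illustration, if the chance of a report per session were constant and equal in all arms, counting every available form would give 6/5 = 1.2 times as many reports per active participant with no true difference.

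**Size if sham participants continue**

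No session is lost in any arm. Session 6 is deferred to T10 in all three, and T9 still has no form.

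**With DESS added at T9**

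Session 6 maps to T9 in all arms. On the schedule that ends at T9, sham coverage rises from 5 of 6 sessions to 6 of 6.

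**The case against.** The strongest reply is that this may be a missing tick and not a missing form. The harms wording already covers T9, and the article does not show which of the two reflects practice. That stands, and it is why the fix allows for correcting the table alone.

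Three stronger readings are tempting, and the article does not support them.

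1. A reader might infer that session 6 effects are lost in every arm. They are not: in ISF1 and ISF2 the T10 set-up form comes before session 7 and can record them.
2. A reader might infer that, because T9 is the only assessment visit with a planned sham comparison, there are no sham-controlled harms data. That planned comparison concerns PROs and neurophysiology. DESS is also scheduled at T3–8 in all arms, so T4 to T8 give five post-exposure controlled forms covering sessions 1 to 5.
3. A reader might take the sham loss as certain. It depends on the Sham row of Table 2 and the Randomization section, which the abstract and the timeline text contradict.

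It is also fair to say that the article announces no between-arm DESS analysis, and that such detail may sit in an analysis plan not shown. Its absence is not criticised here; the point concerns which data are collected.

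Finally, the Trial status section expected data collection to finish by the end of 2021, and the article appeared in November 2022. Few participants, if any, may still be ahead of T9. This limits what a schedule change can recover. It does not remove the need to state what was collected.

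**Conclusion.** The point holds in a limited form. Table 2 omits DESS at a visit that the harms section's wording includes, and the two must be reconciled on any reading. As scheduled, controlled harms data that all arms share reach session 5 only.

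For session 6 the consequence depends on an unresolved contradiction. If the sham arm ends at T9, 1 of 6 sham sessions (17%; 30 of 180 at n=30) has no harms report while the active arms have one at T10, so ascertainment of block 1 is unequal. If sham participants continue, the effect is a deferral to T10 in every arm.

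The conclusion rests on the form being completed before training, which follows from the set-up wording, and on each form covering the interval since the previous one, which is assumed. It is a modest gap that is cheap to close. It does not mean that the controlled harms comparison is absent.

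**What to change.** 1. Add a DESS tick at T9 for all arms in Table 2, with the form completed on the iPad at the EEG set-up already planned for that visit. If the form was in fact given at T9, correct the table to show it. Session 6 is then ascertained at the same visit in every arm.
2. Reconcile the sham arm's schedule after T9 across the abstract, the Randomization section, the Participant timeline text and the Sham row of Table 2.
3. For participants already past T9 without a form, restrict any between-arm harms comparison for block 1 to the forms common to all arms (T4 to T8), treat T3 as pre-exposure, and report that session 6 is not covered on an equal basis.

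The cost is one 43-item self-report at an existing visit, with no extra visit. For completed participants there is only the reporting statement, since a form that was not given cannot be recovered.
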